# A randomized controlled trial: Comparison of 14 and 24 French thoracic drainage after minimally invasive lobectomy – MZ 14-24 study

**DOI:** 10.1016/j.heliyon.2023.e22049

**Published:** 2023-11-07

**Keywords:** Thoracic surgery, Uniportal VATS, Lung surgery, Lobectomy, Chest tube, Thoracic drainage

## Abstract

**Background:**

The optimal placement of a chest drain after video-assisted minimally invasive lobectomy should facilitate the aspiration of air and drainage of fluid. Typically, a conventional 24Ch polyvinyl chloride chest drain is used for this purpose. However, there is currently no scientific literature available on the impact of drain diameter on postoperative outcomes following anatomical lung resection.

**Methods:**

This is a prospective, randomized, phase-1 trial that will include 40 patients, which will be randomly assigned into two groups. Group 1 will receive a 24 French chest drain according to current standards, while group 2 will receive a 14 French drain. Primary endpoint of the trial is the incidence of postoperative drainage-related complications, such as obstruction, dislocation, pleural effusion, and reintervention. Secondary endpoints are postoperative pain, chest drainage duration, incidence of complications, and hospital length of stay. The study aims to determine the number of subjects needed to achieve a sufficient test power of 0.8 for a non-inferiority study.

**Discussion:**

Thoracic surgery is becoming more and more minimally invasive. One of the remaining unresolved problems is postoperative pain, with the intercostal drain being one of the main contributing factors. Previous data from other studies suggest that the use of small-bore drains can reduce pain and speed up recovery without an increase in drain-related complications. However, no studies have been conducted on patients undergoing anatomic lung resections to date. The initial step in transitioning from larger to smaller drains is to establish the safety of this approach, which is the primary objective of this trial.

Trial registration: The study has been registered in the German Clinical Trials Register.

Registration number: DRKS00029982.

URL: https://drks.de/search/de/trial/DRKS00029982.

## Background

1

Following video-assisted minimally invasive lobectomy, the placement of a chest drain is a common practice to evacuate air and fluid from the pleural cavity. However, there is a lack of eveidence and randomized studies investigating the optimal drain size for anatomic lung resections and its impact on patient recovery. While some studies support the use of small-bore drains in other lung and thoracic conditions, many surgeons still prefer larger-bore drains due to concerns about potential obstruction [1]. However, bigger drains have been related with increased risk of pain and therefore increased patient discomfort [[2], [3], [4], [5]].

Recent studies [6] have shown no significant difference in complications between small- and large-bore drains, and studies reporting results after pleurodesis [7,8] suggest that small-bore drains are equally effective without an increased risk of obstruction. The use of small-bore drains is already a standard of treatment for conditions like pneumothorax [9], but there is currently no uniform guideline for the appropriate size of thoracic drainage [10]. Similarly, in the treatment of pleural empyema, studies have found no significant difference in disease-associated deaths and required interventions based on drain size, with small-lumen drains being equally effective and associated with less pain [11].

The German Society for Thoracic Surgery Delphi consensus on the management of thoracic drains indicates that a conventional 24 French (F) chest drain is commonly used after lung lobectomy [12]. A recently published nationwide survey confirmed that over 85 % of German thoracic surgeons use 24 F drains or larger [13].

The whole field of thoracic surgery has emensly evolved during the past decade. Complex lung resections are now performed through a 3–4 cm incision. It is contradictory to the principles of minimally invasive surgery to use a drain that is nearly as large as the incision itself, especially considering the very well known relation between chest drains and postoperative pain. Pain still remains one of the unresolved issues following thoracic surgery. Less postoperative pain means better lung function, faster recovery, faster return to normal life. Reducing postoperative pain could positively impact every aspect of our current postoperative pathways on thoracic surgery.

We therefore consider it vital to address this issue in a formal trial. The aim of this phase I trial is to establish the safety of using a small-bore drain in these procedures and gain more insight on the effect of smaller drains on postoperative pain following thoracoscopic anatomic lung resections.

## Methods

2

### Study participants

2.1

A total of 40 patients undergoing uniportal video-assisted thoracoscopic lobectomy (uVATS) at the Center for Thoracic Diseases (CTD) will be recruited for this study. Patients meeting the inclusion criteria and providing informed consent will be enrolled. The sample size of 40 patients would allow us to analyze 20 patients on every group. This number is considered appropriate for Phase I trials in order to collect the necessary safety information and perform subsequent sample size calculations for a larger efficacy trial. In order to analyze 40 patients and taking into account the increasing number of anatomic segmentectomies performed and our conversion rate, we assume that around 100 patients need to be screened (Fig. 1).

**Fig. 1 fig1:**
[figure not shown]
Trial flowchart.

### Inclusion criteria

2.2

Patients over 18 years of age scheduled to undergo a lobectomy using uVATS for benign or malignant lung lesions, including primary lung cancer or pulmonary metastasis, will be eligible for inclusion in the study.

### Exclusion criteria

2.3

Patients who do not undergo lobectomy using minimally invasive techniques, and patients undergoing other types of lung resection (wedge resection, segmentectomy, bilobectomy/pneumonectomy) will be excluded. Patients with a history of congenital or acquired coagulopathy, use of direct oral anticoagulants, deviation from standard postoperative pain management regimen, or chronic analgesic therapy will also be excluded.

The study will randomize the 40 patients into two groups of equal size. Group 1 (control group) will consist of 20 patients who will receive a conventional 24 French (24F) chest drain according to current standards. In Group 2, a 14 French (14F) drain will be used (intervention group), which will be placed intraoperatively through the same access required for lung resection. The 14F drain will be secured to the skin with a separate suture, following the same technique as the placement of the 24F drain.

Drain removal is indicated by a board certified thoracic surgeon during the morning round on every postoperative day. In order for the drain to be removed there must not be any air leak during the past 24 h before the morning ward round and the fluid drainage has to be less than 5 ml/kg/24 h [14].

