## Implementation

4

The physicians at the Center for Thoracic Diseases (CTD) will strictly follow the established clinical routine for surgery preparation, diagnostics, and pre-admission procedures. Informed consent will be obtained from all participating patients by the physicians. Patients who provide consent for surgery will be informed about the opportunity to participate in the study, provided they meet the inclusion criteria and have no exclusion criteria. During the consenting process the benefits and risks will be thouroughly explained, and enrollment will proceed after written consent has been obtained.

All referrals for surgery are discussed in the local multidisciplinary team meeting. The choice of the surgical approach is always determined by a board certified thoracic surgeon. All surgical procedures will be performed by or supervised by a board certified thoracic surgeon with experience in uniportal thoracoscopic lung resections (>100 thoracoscopic anatomic lung resections). Three consultant surgeons fulfill these criteria in our department. The treatment method implemented will be based on randomization, with one group receiving 14F drainage and the other group receiving 24F drainage. The consultant surgeon performing or supervising the procedure will be responsible for deciding if the patient is eligible for randomization. It is our institutional practice to ventilate the lung at the end of the procedure and perform an underwater air leak test in order rule out major air leaks and check the bronchial closure.

If the thoracic consultant considers the patient eligible for randomization, the randomization process will take place before insertion of the drain at the end of the procedure. The drains will be inserted through the surgical incision into the chest cavity, and their positioning will be visually confirmed before securing them to the skin using a suture made with Supramid 0 thread from B.Braun. Standardized sutures will be used to close the muscle, subcutaneous tissue, and skin. Both groups' drains will be connected to a digital thoracic drainage system (Thopaz from Medela Healthcare, Switzerland) with a suction of −8 cm H2O (physio mode). All electronic suction devices will be calibrated before use as recommended by the manufacturer.

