### Drop-out

4.1

There are multiple factors that can result in the discontinuation of an individual's participation in the study, such as the participant's voluntary withdrawal or failure to meet the inclusion and/or meeting the exclusion criteria. However, it is important to note that these circumstances do not fall within the category of drop-outs, since no randomization takes place prior to these occurrences.

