### Data management and protection

4.4

The data collected will be stored digitally on data storage devices at the Thoracic Surgery department of the University Medicine Mainz. Data security will be ensured by following the data protection guidelines of the University Medical Center Mainz and complying with legal requirements, including the General Data Protection Regulation (GDPR).

The study will be conducted in accordance with the current version of the Declaration of Helsinki. The study protocol has been approved by the Ethics Committee of the district medical council of Rhineland-Palatinate (approval Nr. 2021–15994). All patient information, including names and other confidential data, will be treated with medical confidentiality and will be subject to the provisions of the State Data Protection Act of Rhineland-Palatinate and the Federal Data Protection Act (LDSG BW and BDSG). Patient data will only be shared in pseudonymized form, and original documents will not be accessible to third parties.

The data will be stored for a period of 25 years, in compliance with the provisions of the Good Clinical Practice (GCP) regulation of August 9, 2004. Participation in the study is voluntary, and patients have the right to withdraw their consent at any time without providing a reason and without any negative impact on their medical care. Before the study commences, participants will be provided with written and verbal information about the nature and scope of the planned investigation, including potential benefits and risks to their health. Their consent will be documented through the signing of an informed consent form. In the event of withdrawal from the study, any data already collected will be destroyed, or the patient will be asked for permission to analyze the existing materials.

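### As worded, the exclusion for deviating from the postoperative pain regimen falls after randomisation; this contradicts section 4.1, can bias the comparison and leaves 20 analysed per arm unassured

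*Protocol article*

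**What the plan says.** - **Exclusion (2.3).** After coagulopathy and direct oral anticoagulants, the list closes with "deviation from standard postoperative pain management regimen, or chronic analgesic therapy will also be excluded".
- **Time of randomisation (4, Implementation).** If the consultant finds the patient eligible, "the randomization process will take place before insertion of the drain at the end of the procedure".
- **Drop-out (4.1).** Participation may end through the "participant's voluntary withdrawal or failure to meet the inclusion and/or meeting the exclusion criteria". The section then says that "these circumstances do not fall within the category of drop-outs, since no randomization takes place prior to these occurrences".
- **Withdrawal (4.4).** Patients may withdraw consent at any time. "In the event of withdrawal from the study, any data already collected will be destroyed"; the same sentence continues with an alternative, namely asking the patient to allow analysis of what exists.
- **Numbers.** Section 2.3: "The study will randomize the 40 patients into two groups of equal size". Section 2.1: "The sample size of 40 patients would allow us to analyze 20 patients on every group". Section 4.3 prepares 40 envelopes. The one stated allowance for losses concerns screening: "taking into account the increasing number of anatomic segmentectomies performed and our conversion rate, we assume that around 100 patients need to be screened".
- **Outcomes and data.** Drain-related interventions are primary (3.1). Pain, scored twice daily for three days, is secondary (3.2). Analgesic medication is recorded daily (4).

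**The concern.** An exclusion criterion should rest on facts fixed before allocation. Read plainly, this one rests on what happens on the ward afterwards. If it is applied, randomised patients leave the analysis because of an event that the allocated drain may have influenced.

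The article supplies two reasons to expect such influence. The Background links larger drains to more pain. The Discussion says that small-bore drains obstruct or kink more often and that the resulting repositioning adds discomfort. Either could plausibly change a patient's analgesia. The patients removed would then tend to be those with more pain, and possibly those with drain problems.

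These are the two results the trial is meant to hand on. Complication data are to size a non-inferiority trial (4.3), and the pain scores help decide whether a large pain trial follows (7). Section 4.1 hides the problem, because it states that losses of this kind cannot follow randomisation.

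**Working it through.** **1. Order of events**

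| Event | Section | Relative to randomisation |
|---|---|---|
| Consultant judges eligibility | 4 | before |
| Envelope opened | 4, 4.3 | randomisation |
| Drain inserted | 4 | after |
| Postoperative analgesia given; deviation can be seen | 2.3, 4 | after |
| Withdrawal of consent | 4.4 | any time, so also after |

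Section 4.1 says that exclusions and withdrawals are not preceded by randomisation. The fourth row contradicts this on the plain reading of section 2.3. The fifth row contradicts it on any reading.

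**2. The planned number**

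40 / 2 = 20 per arm reproduces the plan's figure, but only with no loss after randomisation. The allowance of about 100 screened covers segmentectomies and conversions, which arise before randomisation.

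The article gives no deviation rate, so a common rate d is assumed in both arms. Expected analysed per arm = 20(1 − d). P(all 40 kept) = (1 − d)^40. Number to randomise per arm to keep 20 = 20 / (1 − d), rounded up.

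| d (assumed) | Expected per arm | P(all 40 kept) | Needed per arm |
|---|---|---|---|
| 5% | 19 | 0.95^40 = 13% | 22 |
| 10% | 18 | 0.90^40 = 1.5% | 23 |
| 20% | 16 | below 0.1% | 25 |

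Even at d = 1%, P(all 40 kept) = 0.99^40 = 67%.

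**3. Pain: illustration with assumed inputs**

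True means are 4 (24F) and 3 (14F), SD 2, normal scores, and everyone above a cut-off c is removed. None of these values comes from the article. With a = (c − μ)/2, the mean of those kept is μ − 2·φ(a)/Φ(a).

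For c = 6:
- 24F: a = 1, 15.9% removed, mean kept = 4 − 2(0.2420/0.8413) = 3.42.
- 14F: a = 1.5, 6.7% removed, mean kept = 3 − 2(0.1295/0.9332) = 2.72.
- Observed benefit = 3.42 − 2.72 = 0.70 instead of 1.00.

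For c = 5 the observed benefit is 0.56, and for c = 7 it is 0.83. If the true means are equal, the same rule produces no bias.

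**4. Complications: illustration**

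The Discussion cites obstruction rates of 8.1% (small-bore) and 5.2% (large-bore). Suppose that 50% of patients with a complication and 10% of the others are removed (assumed). Observed rate = 0.5p / [0.5p + 0.9(1 − p)].
- 8.1%: 0.0405 / (0.0405 + 0.8271) = 4.7%.
- 5.2%: 0.0260 / (0.0260 + 0.8532) = 3.0%.
- The difference falls from 2.9 to 1.7 points.

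If 10% are removed regardless of complications, both rates are unchanged.

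**5. Precision with zero events in an arm**

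Upper end of the two-sided 95% exact interval, 1 − 0.025^(1/n): 16.8% at n = 20 and 20.6% at n = 16. The one-sided 95% bounds, 1 − 0.05^(1/n), are 13.9% and 17.1%.

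**The case against.** **The criterion may mean something known beforehand.** It stands in a list of patient facts, between anticoagulant use and chronic analgesic therapy. Eligibility is judged immediately before the envelope is opened. It could describe patients already known not to be going onto the standard regimen, and that would fit section 4.1. This reading is possible, but the text does not state it, and chronic analgesic therapy is already listed separately. It also leaves section 4.1 wrong about withdrawal.

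**Dependence on drain size is inferred.** No section ties regimen deviation to drain size, and what counts as a deviation rests on a standard operating procedure that is not shown. The two mechanisms also push towards opposite arms: pain towards 24F, drain problems towards 14F. This stands, so the direction cannot be asserted. The link to lost primary events is weaker still, because nothing says that irrigating or repositioning a drain takes a patient off the regimen.

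**Analysis sets and replacement rules belong elsewhere.** This is correct, and their absence from an article is no finding. The point here is a positive statement in section 4.1 that conflicts with sections 2.3 and 4.4.

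**Section 4.4 does not make destruction the default.** A reader who stops at the first half of the sentence might infer that it does. The sentence offers two options and ranks neither.

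**Conclusion.** The contradiction stands. On their plain wording, sections 2.3 and 4 allow an exclusion after randomisation that section 4.1 says cannot occur, and section 4.4 contradicts section 4.1 on withdrawal. Followed as written, the rule can bias the pain comparison and possibly the complication comparison. With 40 envelopes for 40 analysed patients, 20 per arm cannot be assured.

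A reader might go further and conclude that the comparison is biased and that 20 per arm will not be reached. The documents do not support that. Both outcomes require that deviations occur and that patients are in fact removed for them. Bias also requires that exclusion be related to the outcome. The fall from 1.0 to 0.70 points shows what is possible under the assumed means, SD and cut-off; it is not an estimate for this trial. The trial is descriptive and has no power calculation, so the shortfall costs precision rather than a stated power.

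**What to change.** 1. In section 2.3, limit the pain-regimen criterion to facts known before randomisation. Deleting it is unnecessary, since that would also drop a legitimate exclusion known before surgery.
2. State that every randomised patient is analysed in the assigned arm for the primary and all secondary outcomes.
3. Report regimen deviations and analgesic use by arm. Analgesic medication is already recorded daily.
4. Correct section 4.1 to say that withdrawal can occur after randomisation.
5. In section 4.4, make asking permission to keep collected data the first step, with destruction if the patient declines.

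The cost is a short amendment of wording, with no extra patients or procedures. With all randomised patients analysed, 40 randomised again gives 20 per arm, apart from patients who withdraw and refuse use of their data. The small downside is that pain scores will include some patients on non-standard analgesia; the report by arm makes this visible. None of this changes the analgesia that any patient receives.

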### Trial timeline

2.4

The recruitment phase has been estimated at 12 months. The overall trial duration will be two weeks after the last patient has been discharged.

## Assessment of outcomes

3

### Primary outcome measures

3.1

Drain related complications: includes irrigation of the drain, repositioning of the drain, placement of an additional drain, re-VATS (video-assisted thoracoscopic surgery), placement of a new drain after previous drainage.

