Daily clinical data will be collected, including the fever curve to monitor body temperature, pain intensity using the Numerical Analog Scale (NAS) recorded twice daily, analgesic medication administered, quantity and quality of secretion per 24 h (recorded by nursing staff at 6 a.m.), and assessment of parenchymal fistula (recorded during the morning visit at 7:45 a.m. based on the graph displayed in the last 24 h). Incision wound checks will be performed on the day of surgery, at discharge, and during follow-up visits at the outpatient clinic, usually scheduled within 14 days after discharge.

Postoperative procedures, including drainage and pain management, will follow our standard operating procedure for postoperative care after thoracic surgery. Patients following anatomic lung resections are usually monitored for 24 h on a high dependency or intensive care unit. If the immediate postoperative period is uneventful the patients are usually transferred on the ward on the first postoperative day. The patients are usually discharged one day after drain removal. A final follow-up visit is part of our postoperative care standard operating procedure and usually takes place 2 weeks after surgery in the outplatient clinic.

As part of routine clinical practice, patients typically receive three peripheral nonsteroidal analgesics and a perivertebral pain catheter with 0.375 % Ropivacain at a rate of 10 ml/h. A chest X-ray (PA view) will be performed on the first postoperative day, immediately prior to drainage removal, and during follow-up visits at the outpatient clinic. If the X-ray shows any pathological findings, further tests may be requested as indicated.

Before discharge, patients are informed to visit the Department of Thoracic Surgery if they experience any complaints.

A risk-benefit analysis has determined that the placement of a postoperative chest drain is a routine procedure without additional burden to the patient. While treatment with a 24F chest drain is a standard procedure with no increased risk, treatment with a 14F chest drain may result in more postoperative interventions due to potential complications such as pneumothorax or drain occlusion. However, the medical staff at CTD is highly senzibilized to these possibilities and prepared to promptly react if such events occur. After the surgery, all patients are monitored on the intermediate care unit overnight under close supervision by the medical staff.

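### The primary endpoint is stated inconsistently: the abstract counts drain events and reintervention, section 3.1 lists only interventions, and the safety rule uses a third wording

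*Protocol article*

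**What the plan says.** Three places in the protocol article describe the event that the trial is meant to count.

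- **Abstract, Methods:** "Primary endpoint of the trial is the incidence of postoperative drainage-related complications, such as obstruction, dislocation, pleural effusion, and reintervention". Three of the four items are clinical events; the fourth is an action.
- **Section 3.1, Primary outcome measures:** the endpoint "includes irrigation of the drain, repositioning of the drain, placement of an additional drain, re-VATS", and, as a fifth item, "placement of a new drain after previous drainage". All five are things done to the patient. Obstruction, dislocation and effusion are not named.
- **Section 4.2, Safety:** the study stops if complications, or a need to drain the pleural cavity again, occur in more than 20% of the first ten experimental patients. This wording matches neither of the other two, and the complications meant are not specified.

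Two further places bear on the point. Section 2.3 sets two conditions for taking the drain out: daily fluid output under a stated limit and, as regards air, that "there must not be any air leak during the past 24 h before the morning ward round". Section 3.2 lists drainage time in days as a secondary outcome and does not say how a drain removed because it failed is handled.

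**The concern.** The stated purpose of the trial is to establish the safety of the smaller drain (sections 1, 6 and 7). Its data are also meant to size a later non-inferiority trial (abstract and section 4.3). Both uses need one event definition, and the article gives more than one.

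The gap lies in events that are managed without any of the five listed actions: an effusion seen on X-ray and observed, a displaced drain that is taken out, or a blocked drain that is removed and not replaced. The last is not far-fetched on the article's own account. Section 5 says that obstruction or kinking of a small drain leads to removal, with repositioning only a possibility. A blocked drain can also show no air leak and little fluid, and the article describes no patency check. Such a patient has an event under the abstract and none on the 3.1 list, and contributes a short drainage time.

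With few events expected, a handful of such patients could change both the safety result and the rate carried into the next sample size calculation.

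**Working it through.** **Step 1. Set the definitions side by side.**

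| Course | Abstract | Section 3.1 list | Section 4.2 wording |
|---|---|---|---|
| Obstruction, drain irrigated | event | event | unclear |
| Obstruction, drain removed, no later drain | event | not listed | unclear |
| Obstruction, drain removed, new drain later | event | event | event |
| Dislocation, drain repositioned | event | event | unclear |
| Dislocation, drain removed, no later drain | event | not listed | unclear |
| Effusion on X-ray, observed only | event | not listed | unclear |
| Irrigation without a confirmed obstruction | only if it counts as reintervention | event | unclear |

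The abstract and 3.1 agree whenever an event leads to a listed action. They part when it does not, and possibly for irrigation alone. The entries marked unclear turn on what 4.2 means by complications.

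**Step 2. Weight of one patient.** The only stated figure to reproduce is the allocation (section 2.1): 40/2 = 20 per arm, which agrees. No power calculation stands behind the 40. One reclassified patient changes an arm's rate by 1/20 = 5 percentage points.

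**Step 3. Scale of the event counts.** Section 5 cites obstruction risks of 8.1% (small-bore) and 5.2% (large-bore). These are for obstruction alone, not for the composite, so they serve only as a scale.

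- 14F: 20 × 0.081 = 1.62 expected obstructions
- 24F: 20 × 0.052 = 1.04 expected obstructions
- Difference in risk: 8.1 − 5.2 = 2.9 points, less than the 5 points that one patient carries

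For section 4.2, 20% of ten is 2, so the limit is passed at 3 events. Whether one patient counts can decide it.

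**Step 4. Sensitivity of the follow-on trial (illustration only).** The article gives power 0.8. Assumed here: one-sided alpha 0.025, a 10-point margin, the cited obstruction risks as true rates, and a share s of obstructions, equal in both arms, that end in removal alone and are not counted.

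n per arm = (1.960 + 0.842)² × [pC(1 − pC) + pT(1 − pT)] / [margin − (pT − pC)]²

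- s = 0: pC = 0.052, pT = 0.081; 7.849 × 0.1237 / 0.071² gives 193
- s = 0.25: 122
- s = 0.5: pC = 0.026, pT = 0.0405; 7.849 × 0.0642 / 0.0855² gives 69
- s = 0.75: 30

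Going from s = 0 to s = 0.5, n per arm falls from 2203 to 400 at a 5-point margin and from 67 to 28 at 15 points. The article supplies neither s nor the margin. The calculation shows only that the planned use of the rate is sensitive to what is counted.

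**The case against.** The best defence is that both lists are open and describe the same thing, with 3.1 as the working form of the abstract: irrigation or repositioning answers obstruction or dislocation, a further drain answers effusion, and re-VATS is a reintervention. That shows a large overlap, and it stands to that extent. It does not remove the problem. If the lists are closed, they differ. If they are open, neither settles whether an untreated event counts.

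A reader might go further and infer that 3.1 hides 14F failures and so favours the small drain on the primary outcome and on drainage time. The article does not support that:

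- The fifth item in 3.1 captures a failed drain that later needs re-drainage, so only failures with no later listed action are lost.
- The removal criteria are necessary conditions, and a board certified surgeon decides. Section 4 schedules a chest X-ray immediately before removal and at follow-up, which may reveal some failures.
- Untreated events may still be recorded among the secondary complications and the radiological and clinical findings of section 3.2, although this does not make them primary events.
- The direction is open. Section 4 warns that "treatment with a 14F chest drain may result in more postoperative interventions due to potential complications such as pneumothorax or drain occlusion" and says that staff are alert to this. That could raise the number of interventions, and so the counted events, in the 14F arm.

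A reader might also fault the absence of pneumothorax. Without an intervention it is in neither list, so adding it would be a preference and would resolve no contradiction. A choice of definition after the data are seen is possible, but nothing shows that it is intended, and section 4.3 plans descriptive and exploratory analyses only.

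Finally, adjudication detail is properly left to a fuller document. The point here is different: the article prints its primary endpoint twice, and the two statements disagree.

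**Conclusion.** The concern holds as an inconsistency in the primary safety endpoint. An obstruction, dislocation or pleural effusion that leads to none of the five interventions in 3.1 is an event under the abstract and is not on the 3.1 list. This includes a blocked drain removed and not replaced. A patient who later needs a new drain does count under 3.1. Section 4.2 adds a third wording that cannot be mapped with confidence onto either.

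The certain part of the size is 5 points per affected patient in an arm of 20. How many patients would be affected, and whether they would fall more in one arm, cannot be derived from the article. The expected obstruction counts rest on the risks cited in section 5, and the follow-on sample sizes rest also on an assumed alpha, margin and uncounted share; none of them measures a bias. The point merits correction because these rates are meant to support the safety conclusion and to size the next trial.

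**What to change.** 1. Use one definition in the abstract and in 3.1: any drain obstruction, dislocation or drain-related pleural effusion, or any intervention now listed in 3.1.
2. State that a drain removed because of malfunction is scored as an event, whether or not it is replaced.
3. Report each component by arm, from the clinical and radiological findings already collected under section 3.2.
4. Reconcile the event wording in 4.2 with this definition, leaving the stopping rule itself unchanged.
5. As a secondary point, flag drains removed for malfunction in the drainage-time analysis and count the days with a replacement drain. Counting replacement days alone would not deal with a blocked drain that is removed and not replaced, which is why the flag is needed.

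The cost is protocol wording and a field recording the reason for drain removal. There is a small downside: the reported event rate will be somewhat higher, and events without an intervention need some judgement to score, whereas the items now in 3.1 are recorded procedures. Reporting the components separately keeps the intervention-only count visible.
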